### Procedure

Eligible participants will be identified through the different sites by a case manager, mainly, by the participant’s general practitioner. However, other professionals (i.e., psychiatrist, psychologist or community mental health nurses) with experience in the assessment and diagnosis of depression would be also able to refer participants to the study. These professionals will verify inclusion/exclusion criteria and will inform patients about the study. Participants who confirm their interest in participating, will be contacted by phone within 1 week to schedule the first assessment visit (face-to-face). Each site will designate a highly trained psychologist who will conduct the first face-to-face visit in order to confirm that participants met inclusion/exclusion criteria and to obtain the written informed consent. Participant’s assessment will be recorded in the electronic Case Report Form (e-CRF). In this assessment visit, and regardless of the treatment arm the patient will be assigned to, the second face-to-face assessment visit (week 8) will be booked. Randomization to one of the two conditions (i.e., iFightDepression tool + TAU or internet-based psychoeducation + TAU) will be electronically performed by the e-CRF once the patient data is introduced. The researcher who conducts assessment visits will remain blind to participant’s allocation. After the first visit, participants in both arms will received an email with instructions to be followed. The intervention group will receive instructions to create an account and to work within the iFD tool. In addition, the intervention group will receive a telephone call to make sure that participants activated successfully their user accounts. Then, they will be contacted bi-weekly by a mental health professional (specialized nurse or psychologist), to work through the material and to provide technical support). During the 8 weeks of the trail all participants will be follow-up by e-mail in order to complete the PHQ-9 and RDQ. Participants will have to complete the PHQ-9 and the RDQ again at week 12. The study protocol was developed in accordance with the SPIRIT (Standard Protocol Items: Recommendations for Interventional Trials) guidelines [17]. A flowchart of participants is shown in Fig. 1.

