### Study objectives

The aim of this double blind, randomized controlled trial (RCT) is to examine the efficacy of the iFightDepression as an add-on to treatment as usual (TAU) for patients with mild to moderate depressive symptoms versus internet-based psychoeducation plus TAU. The primary outcome measure will be changes in depressive symptoms as measured with the Hamilton Depression Rating Scale [16]. Secondly, we aim at examining the effects of this intervention on other variables including quality of life and functioning.

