## Methods

### Design

We designed an 8-week, double-blind, randomized controlled trial, with two treatment arms: iFightDepression tool + TAU and internet-based psychoeducation + TAU. Participants will be randomly allocated (1:1) after the first assessment visit. Randomization will be performed electronically by an independent study researcher. Participants in both treatment arms will be followed via internet during a 12-week period.

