#### Active control group (internet-based psychoeducation + TAU)

Internet-based psychoeducation consists of a webpage containing information about MDD and healthy habits. This webpage (www.ifightdepression.com) was also designed by the EAAD consortium, and unlike the tool, workshops and tasks are lacking. The psychoeducative content of this website is restricted to information regarding healthy habits (healthy eating, physical activity, positive social contact and daily organization). In addition, information on the following topics is included: what is depression, signs and symptoms, diagnosing depression, subtypes of depression, brain function in depression, causes and an overview of depressions treatment (both pharmacological and psychological). Participants on this condition can also complete the online PHQ-9. This is an open-access webpage (i.e., a username and password are not required). Participants allocated to this condition will receive an e-mail with the page link and will be instructed to navigate freely throughout their content. As in the intervention group, TAU consists of monthly visits to the GP together with pharmacological treatment (if needed).

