## Discussion

The present study aims at evaluating the efficacy of an internet-based self-management tool for moderate to mild depression compared with internet-based psychoeducation. Confirming the efficacy of the iFightDepression tool will entail important implications. As IFD could be easily prescribed it could potentially reach patients that usually remain untreated or have to wait for long-periods to receive psychological treatment. In addition, the availability of the both interventions in three different languages (Spanish, Catalan and Basque) aims at facilitating participant’s adherence. A strength of our study is that the recruitment will mainly take place in general practices, were patients with mild to moderate depression symptoms are often treated.

The risk of dropout constitutes one of the potential major obstacles of our study. We’ve tried to mitigate this by expanding our recruitment area to public health-care facilities located in three large areas of Spain (Catalonia, Madrid and Basque Country) and by providing specific language versions of the iFD tool and the psychoeducation web-page. As commented before, the design of our study privileges a naturalistic approach and therefore, participants will be recruited from primary care facilities in which most patients with mild/moderate symptoms of depression are visited and participants with concomitant ant depressive medication will be allowed in the study. Considering that the effects of the concomitant medication may impact our findings, a sub-analysis evaluating the potential effects of antidepressant will be conducted and participants will be excluded from the study if drastic changes in their medication took place during the study period.

In summary, the present study aims to provide evidence in regards to iFD tool as an add-on approach for individuals presenting mild to moderate symptoms of depression. Counting on a tool like iFD will facilitate its use in the public health care system, representing a treatment approach that can potentially reach a large amount of patients avoiding long waiting lists.

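### The trial is called double-blind but describes only a blinded assessor, and it tests iFD with professional guidance, not the self-management tool alone

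*Protocol article*

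**What the plan says.** The protocol article uses the double-blind label in the Abstract (Background), in Study objectives and in Design. Design reads: "We designed an 8-week, double-blind, randomized controlled trial, with two treatment arms: iFightDepression tool + TAU and internet-based psychoeducation + TAU". Study objectives reads: "The aim of this double blind, randomized controlled trial (RCT) is to examine the efficacy of the iFightDepression as an add-on".

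The only statement of who is blinded is in Procedure: "The researcher who conducts assessment visits will remain blind to participant’s allocation".

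Procedure also describes contact for the intervention arm: "In addition, the intervention group will receive a telephone call to make sure that participants activated successfully their user accounts". It continues: "Then, they will be contacted bi-weekly by a mental health professional (specialized nurse or psychologist), to work through the material"; the same contact also covers technical help. For controls, the section on the active control group says: "Participants allocated to this condition will receive an e-mail with the page link and will be instructed to navigate freely throughout their content". That page is open to anyone, needs no account, and has no workshops or tasks.

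The section describing the intervention arm covers modules, worksheets, languages, the online PHQ-9 and usual treatment. It does not list the professional contact. The Discussion gives the purpose of the study as "evaluating the efficacy of an internet-based self-management tool for moderate to mild depression compared with internet-based psychoeducation".

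**The concern.** Two stated properties of the trial do not match what it delivers.

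The first is blinding. A double-blind label tells readers that participants, as well as assessors, are kept unaware of allocation. That matters most for outcomes that participants rate themselves. If only the assessor is blinded, the label overstates the protection of those outcomes.

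The second is the intervention. The aim and the arm name speak of a tool, and the article calls it self-management and easy to prescribe. The arm actually receives the tool together with a nurse or psychologist who goes through it with the participant. A positive result would then be read as evidence for a tool that needs little professional time, which this comparison cannot provide.

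**Working it through.** No figure in the plan bears on this point, so the check sets the sections side by side.

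**Step 1. Who is blinded as described?**

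| Party | What the article gives | Blinded? |
|---|---|---|
| Researcher at assessment visits | Stated to be blind (Procedure) | Yes |
| Nurse or psychologist contacting participants | Contacts the iFD arm only, about its material (Procedure) | No; must know the allocation |
| Participants | No statement. They get either an account, a call, regular contacts and worksheets, or a link to an open page | Not described, and doubtful |

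**Step 2. Which outcomes does this cover?** Sources: Table 2, Primary outcome measure and Secondary outcome measures.

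| Outcome | Rated by | When | Protected by assessor blinding? |
|---|---|---|---|
| HDRS (primary) | Clinician | Baseline, post-intervention | Yes |
| PHQ-9, RDQ | Participant | Baseline, weeks 2, 4, 6, post-intervention, week 12 | No |
| EQ-5D | Participant | Baseline, post-intervention | No |
| CGI-S, patient-rated version | Participant | Post-intervention | No |

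At weeks 2, 4, 6 and 12 only PHQ-9 and RDQ are collected. The course during treatment and the follow-up therefore rest entirely on self-report without described participant blinding. FAST and the clinician-rated CGI are left aside, because the article does not name their rater.

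**Step 3. What contact does each arm get?** Sources: Procedure and the two intervention sections.

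| Contact | iFD arm | Control arm |
|---|---|---|
| Starting e-mail with instructions | Yes | Yes |
| E-mail follow-up for PHQ-9 and RDQ | Yes | Yes |
| Face-to-face visit at week 8 | Yes | Yes |
| Monthly GP visits, medication if needed | Yes | Yes |
| Activation call | 1 | None described |
| Nurse or psychologist contact over 8 weeks | 8 / 2 = 4 if every two weeks; 8 × 2 = 16 if twice a week | None described |

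The number of contacts depends on the meaning of bi-weekly. I take every two weeks as the more likely reading, which is an assumption.

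**Step 4. What does the randomised difference estimate?**

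- iFD arm: usual treatment + shared contact + tool + guidance.
- Control arm: usual treatment + shared contact + web information.
- Contrast by design: (tool + guidance) versus web information.

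Usual treatment and the shared contact are offered equally to both arms. No arm has the tool without guidance or guidance without the tool, so the two cannot be separated. The aim and the arm name mention only the tool.

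**The case against.** The case on the other side is substantial, and much of it stands.

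- **The primary endpoint is protected.** HDRS is clinician-administered, and the assessment researcher is stated to be blind. A reader might infer from the mislabelling that the primary outcome is unblinded; the article does not support that. Participant expectation can still colour answers in an interview, but the complaint does not weigh on HDRS as it does on the self-reports, all of which are secondary.
- **Controls are not left without contact.** They share the e-mail follow-up, the week-8 visit and the monthly GP visits. The imbalance is in guidance and the activation call only.
- **Participants may not know which condition is experimental.** Both websites come from the same consortium under the same name, both offer the online PHQ-9, and the comparator is presented as an active control. What participants are told depends on the information sheet, which is not shown. A reader might infer that iFD participants know they are in the experimental arm; that goes beyond the text. What stands is that no participant blinding is described, that the conditions differ visibly, and that the contacting professionals cannot be blind.
- **The guidance is disclosed and legitimate.** Procedure states it openly, the Background says that therapist involvement varies between programmes and cites evidence on guided self-help, and an unguided comparator is a fair choice in a naturalistic design. This answers any claim that the trial can attribute nothing: the package comparison is sound. It does not make the aim, as worded, match the contrast.
- **The benefits are stated conditionally.** Nothing has been concluded yet, and no section claims efficacy without guidance. The wording can therefore be put right before results are reported.

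**Conclusion.** The point holds in two parts. First, the double-blind label is not supported by the procedures. The trial as described is assessor-blinded, with HDRS covered and PHQ-9, RDQ, EQ-5D and patient-rated CGI-S not covered. Second, the randomised comparison is valid for professionally guided iFD versus unguided web psychoeducation, each added to usual treatment. It is not valid for the tool alone, which is how the aim and arm name are worded.

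The imbalance is one activation call plus about four professional contacts, assuming bi-weekly means every two weeks. Its effect on outcome cannot be sized from the article. A reader might infer that contact explains half to all of the planned d = 0.2. That follows only if contact is assumed to be worth 0.1 to 0.2 SD (0.1 / 0.2 = 50%; 0.2 / 0.2 = 100%). The article gives no such figure, and the top of that range is simply the planned effect, so the percentages restate the assumption.

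**What to change.** 1. Replace double-blind with assessor-blinded in the Abstract, Study objectives and Design.
2. Report PHQ-9, RDQ, EQ-5D and patient-rated CGI-S as not participant-blinded, and say so specifically for the week 2, 4, 6 and 12 results.
3. Restate the objective, the arm name and the planned conclusion as *professionally guided iFD + TAU versus unguided internet-based psychoeducation + TAU*, and list the activation call and the bi-weekly contact in the description of the intervention arm.
4. Make no claim for the tool without guidance, including where the Abstract and Discussion speak of ease of prescription and waiting lists.

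These are wording changes only. Arms, sample size, visits and analysis stay as they are. The price is a narrower claim, limited to the guided package.

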**Fig. 1 Fig1:**
[figure not shown]
Flowchart of participants

### Ethical issues

All participants will be provided with an overview of the study’s aims and characteristics summarized in the Participants Information Sheet (PIS). The voluntarily character of the study will be specified, indicating that withdrawal from the study is permitted at any time, without interfering with the usual treatment. Written informed consent will be obtained from all participants before proceeding with randomization. The study will be performed according to the ethical standards stated in the Declaration of Helsinki and its subsequent updates. The Ethics Committee Board of the Parc de Salut Mar approved the study protocol in October 2014. Data registered in the e-CRF will be coded as to ensure the confidentiality of participant’s identity. The access to the code key will be restricted to the principal investigator of the study, and will be stored separately in a safe place.

### Description of the interventions

#### Intervention group (iFightDepression tool + TAU)

IFightDepression (https://tool.ifightdepression.com) is an internet-based self-management tool designed as a complementary intervention to standard care for patients with mild/moderate symptoms of depression. IFD was created by the European Alliance against Depression (EAAD) and is based in cognitive behavioral therapy (CBT). The IDF tool is structured in seven core modules (workshops) relating to behavioral activation (monitoring and planning daily activities), cognitive restructuring (identifying and changing unhelpful thoughts), sleep regulation, mood monitoring, and healthy lifestyle habits. Each module consists of written information, associated tasks and corresponding worksheets to consolidate learning and promote self-monitoring. A guide on how to complete the worksheets is provided in each module. Worksheets can be printed or completed on-line and are saved in the participants profile for latter review. Patients are encouraged to work with the worksheets for an entire week so the whole content of the program is developed to be completed in 8 weeks. An outline of each module can be found in Table 1. In addition, the tool has a “Frequently asked questions (FAQ)” section and a section “About IDF”, in which participants can find information regarding the causes of depression, the use of the tool, and further reading on cognitive behavioral therapy.

**Table 1 Tab1:** Content outline for iFightDepression tool-intervention group

Module	Content/Aim	Worksheet
1 thinking, feeling and doing	Recognizing the relationship between thoughts, feelings and behavior.	Activity Monitoring
2 Sleep depression	Gaining awareness of the influence of sleep on depression.	Sleep Diary
3 Planning and doing enjoyable things	Building up positive activities in the daily life.	Planning Ahead
4 Getting things done	Developing skills for problem solving and to get things done.	Getting things done
5 Identifying negative thoughts	Understanding the link between thoughts and mood, and learning how to recognize cognitive distortions.	Events, Thoughts and Reactions
6 Changing negative thoughts	Learning how to challenge negative thoughts and how to replace them with more positive alternatives.	Thought Challenge
7 Feel better all around: Healthy Lifestyle	Giving tips for developing a healthy lifestyle in general. Including healthy diet, exercise and sleep.	Sleep Worry Planner

For the purpose of this study and to facilitate the recruitment, the IFD tool is available in three languages: Spanish, Catalan and Basque, and patients are allowed to choose among versions according to their language preferences. Participants can access the PHQ-9 at any time, to assess their depression symptoms. A guide for interpreting the PHQ-9 scores is provided. If the patient responds positively to the item regarding suicide (i.e., “Thoughts that you would be better off dead or of hurting yourself in some way”) a message recommending seeking for emergency care will appear on the top of the screen. In addition, emergency contacts for Spain are listed on the website. The use of IDF tool is complementary to TAU which consists of monthly visits with the GP and pharmacological treatment with an ISRSS if needed.

#### Active control group (internet-based psychoeducation + TAU)

Internet-based psychoeducation consists of a webpage containing information about MDD and healthy habits. This webpage (www.ifightdepression.com) was also designed by the EAAD consortium, and unlike the tool, workshops and tasks are lacking. The psychoeducative content of this website is restricted to information regarding healthy habits (healthy eating, physical activity, positive social contact and daily organization). In addition, information on the following topics is included: what is depression, signs and symptoms, diagnosing depression, subtypes of depression, brain function in depression, causes and an overview of depressions treatment (both pharmacological and psychological). Participants on this condition can also complete the online PHQ-9. This is an open-access webpage (i.e., a username and password are not required). Participants allocated to this condition will receive an e-mail with the page link and will be instructed to navigate freely throughout their content. As in the intervention group, TAU consists of monthly visits to the GP together with pharmacological treatment (if needed).

### Study measures

Different types of variables will be collected (see Table 2) including socio-demographic characteristics of the sample (i.e., gender, age, ethnic group, marital status, living arrangements, educational level, employment status and annual income) and an exhaustive clinical history [i.e., age at MDD onset, number of previous MDD episodes, days in inpatient hospitalization (if applied), axis I and axis II diagnosis, and current pharmacological treatment].

**Table 2 Tab2:** Measures used by study period

Measure	Baseline assessments (Face to face)	Week 2 (Online)	Week 4 (Online)	Week 6 (Online)	Post-intervention assessment (Face to face)	12 weeks FU (online)
Demographic information (gender, age, marital status, etc.)	x					
Medical/Psychiatric History	x				x	
MINI (depression and suicide risk sections)	x				x	
Primary outcome measure:						
-HDRS	x				x	
Secondary outcome measure:						
-PHQ-9	x	x	x	x	x	x
-CGI-S					x	
-RDQ	x	x	x	x	x	x
-EuroQol-5D	x				x	
-FAST	x				x	
-Ad hoc satisfaction Questionnaire					x	

*Note*: *MINI* Mine-international Neuropsychiatric Interview, *HDRS* Hamilton Depression Rating Scale, *PHQ-9* Patient health Questionnaire, *CGI-S* Clinical Global Impression-Severity, *CGI-I* Clinical Global Impression-Improvement, *RDQ* Remission from Depression Questionnaire, *FAST* Functioning Assessment Short Test

### Diagnostic variables

Depression symptoms and suicide risk will be assessed using the specific sections of the Mini-International Neuropsychiatric Interview (MINI) [18], a short diagnostic structured interview. In addition, an ad hoc questionnaire was created for accounting for sociodemographic and clinical data.

### Primary outcome measure

The Hamilton Depression Rating Scale (HDRS) [16] will be the primary outcome measure. This is a clinician-administered scale. Each item on the questionnaire is scored on a 3- or 5-point scale, depending on the item.

### Secondary outcome measures

The following instruments will be used to assess other outcomes:

Patient Health Questionnaire (PHQ-9) [19] is an instrument for screening severity of depression according to DSM-IV-TR criteria. The tool rates the frequency of the symptoms during the last 2 weeks using a scale from 0 (not at all) to 3 (nearly every day).

Clinical Global Impression Severity and Improvement (CGI-S and CGI-I; [20]. The CGI-S scale would be used to evaluate the clinical severity of the participant in a scale from 1 to 7 (“normal, not ill at all” to “extremely ill”). Both a patient-rated version and a clinician-rated version will be used. The CGI-Improvement (CGI-I) will be also used, in order to evaluate the improvement between the baseline visit and the post-intervention assessment (from 1:“very much improved” to 7:“very much worse”).

Remission from Depression Questionnaire (RDQ; [21] is a self-reported instrument developed from a patient-centered perspective, including the aspects that they considered as part of depression remission. The RDQ evaluates depressive symptoms, positive mental health and satisfaction with life, well-being and social functioning.

EuroQol-5D questionnaire (EQ-5D-5 [22] is a widely used measure of health-related quality of life. The instrument is composed of two parts. Part one provides a self-reported description of health problems classified into five dimensions and patients have to rate the severity corresponding to each dimension in a 5-point scale. Part two consists of a 10 cm line Visual Analogue Scale (VAS) corresponding to the current state of subject’s health. The lowest extreme of this scale (0) corresponds to the worst imaginable health state, while the highest extreme (100) refers to the best imaginable health state.

Functioning Assessment Short Test FAST [23] is a brief instrument developed to assess the main functioning problems experienced by patients. It comprises 24 items assessing impairment or disability in six areas of functioning: autonomy, occupational functioning, cognitive functioning, financial issues, interpersonal relationships and leisure time. Each item is rated on a 4-point scale (0 = no difficulty, 1 = mild difficulty, 2 = moderate difficulty and 3 = severe difficulty).

An ad hoc satisfaction questionnaire was created for participants allocated to the intervention group.

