**Methods:**

A total of 310 participants with major depression disorder (MDD) will be recruited at four different mental-health facilities in Spain. Participants will be randomly allocated to one of two study arms: iFightDepression (iFD) tool + TAU vs. internet-based psychoeducation + TAU. Both interventions last for 8 weeks and there is a 12 weeks follow up. The primary outcome measure is changes in depressive symptoms assessed with the Hamilton Depression Rating Scale. Additionally, pre-post interventions assessments will include socio-demographic data, a brief medical and clinical history and self-reported measures of depressive symptoms, quality of life, functional impairments and satisfaction with the iFD tool.

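### The satisfaction form exists only for the iFD arm and is scheduled at the week-8 visit where the blinded assessor rates the HDRS, so it can reveal allocation

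*Protocol article*

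**What the plan says.** The Secondary outcome measures section limits the form to one arm: "An ad hoc satisfaction questionnaire was created for participants allocated to the intervention group". The Methods paragraph of the abstract shows what it asks about, since the assessments there include "self-reported measures of depressive symptoms, quality of life, functional impairments and satisfaction with the iFD tool". No counterpart for the psychoeducation arm is described, either there or in the section on the active control group.

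In Table 2 (Study measures) the row "Ad hoc satisfaction Questionnaire" carries a single mark, in the column for the face-to-face visit after the intervention. The second of the two HDRS marks stands in the same column.

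The Procedure section says that at the first visit, whatever the arm, "the second face-to-face assessment visit (week 8) will be booked". On masking it says: "The researcher who conducts assessment visits will remain blind to participant’s allocation". The Primary outcome measure section says of the HDRS: "This is a clinician-administered scale". The Statistical analysis plan section makes the change in HDRS from baseline to 8 weeks the primary outcome.

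**The concern.** The HDRS depends on the judgement of the person who administers it, and keeping that person unaware of the arm protects the comparison. The article recognises this and promises a blind assessor. It then schedules, at the one post-treatment visit that person runs, a form that exists for one arm only and asks about that arm's programme. If the assessor handles or sees the form, its presence points to iFD. Its absence points to psychoeducation, so both arms would be exposed.

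Blinding of the rater carries much of the weight in this design. Although the article calls the trial double-blind, the arms look different from the participant's side. iFD participants create an account, receive an activation call and are contacted every two weeks; controls are e-mailed a link to an open webpage. If the rater learns the arm before scoring, any leaning in the score goes straight into the primary comparison, and no later HDRS is scheduled against which to check it.

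**Working it through.** There is no figure in the plan to reproduce on this point. The check is a cross-reading of the sections, followed by what each way of handling the form would mean.

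1. **Who has the form.** Intervention arm only (Secondary outcome measures). It concerns the iFD tool (abstract), so a control participant would have no use for it.
2. **When it is due.** Table 2 has six time-point columns: baseline, weeks 2, 4 and 6, post-intervention, and the 12-week follow-up. Four are online (weeks 2, 4, 6 and the follow-up) and two are face to face. The form's only mark is in the post-intervention face-to-face column; none is in an online column.
3. **Who runs that visit.** The researcher who is to stay unaware of allocation (Procedure).
4. **What is rated there.** The HDRS, marked at baseline and at this visit only. CGI-S and FAST are marked in the same column.
5. **What is not stated.** Who gives out the form, on what medium, in what order relative to the HDRS, and who sees the completed form.

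The effect on the primary outcome depends on item 5:

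| Handling of the form at week 8 | What the assessor can learn from it before scoring the HDRS | Bias in the HDRS from this form |
|---|---|---|
| Completed online or with other staff, out of the assessor's sight | Nothing | Zero |
| Seen by the assessor only after the HDRS is recorded and locked | Nothing in time | Zero |
| Seen by the assessor before the HDRS is scored | The arm, by presence or absence | Depends on how far the assessor leans; unknown |

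In symbols, the bias in the between-arm difference is p₁·δ₁ − p₀·δ₀. For the iFD arm (1) and the control arm (0), p is the share of HDRS ratings made after the assessor has learned the arm from this form, and δ is the average shift in those ratings. The article gives none of the four quantities. In the first two rows p₁ = p₀ = 0, so the bias is 0. In the third row the p values exceed zero and the δ values are unknown. The size therefore starts at zero and has no upper figure that the documents can supply.

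**The case against.** The strongest reply is that nothing shows the assessor ever sees the form. The abstract lists it among self-reported measures, and the same Table 2 column also holds PHQ-9, RDQ and EQ-5D, so a mark there does not mean that the assessor administers it. Table 2 lists it last, below the HDRS. The e-CRF performs the randomisation while the assessor stays blind, which suggests that allocation is hidden from that person within the system. This is also a condensed article: the order of forms within a visit and viewing rights in the e-CRF commonly sit in the full protocol or a manual.

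Much of this stands, and it limits the claim. Row order does not settle the order of administration, but nothing shows that the form comes first either. Silence on these details is not the finding. What remains is that two stated elements, the schedule and the blinding claim, pull against each other, and no stated safeguard reconciles them.

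Three stronger readings are tempting, and the documents support none of them:

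- **A reader might infer that the form does reveal the arm, and for every participant.** That needs the assessor to see the form, or notice its absence, before scoring the HDRS each time. The article does not say so. It describes no visit pack, and no e-CRF screen on which the form would appear to the assessor.
- **A reader might put a number on the bias.** Assuming that 50% to 100% of iFD visits are revealed and that raters lean by 0.1 to 0.2 SD gives 0.5 × 0.1 = 0.05 to 1.0 × 0.2 = 0.20 SD. Both inputs are pure assumption. The range leaves out zero, which is the result if the form follows the HDRS, and it counts only the iFD arm although absence of the form would also identify controls. Setting 0.20 SD against the d = 0.2 in the sample-size statement is not secure either, because that statement ties d to a pre-post correlation and does not define its scale.
- **A reader might hold that assessor blinding is the only blinding in the trial.** The article claims double-blinding. The visible differences between arms make participant masking hard to rely on, but that is an argument and not something the article states.

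Participants could also mention modules or telephone contacts in the interview. That is a separate route to unblinding, and moving this form would not close it.

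**Conclusion.** The point holds as a risk created by the schedule. A form for the iFD arm only is due at the visit where a researcher who must not know the arm rates the primary outcome, and the article states nothing that keeps the form from that person until the rating is done. As scheduled, it can reveal allocation.

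The bias in the HDRS may be zero and cannot be quantified from the documents. Any bias at all requires that the assessor sees the form or notices its absence, that this happens before the HDRS is scored, and that the knowledge shifts the score. The article settles none of these three conditions. The change is worth making because it is cheap and protects the primary outcome; this is not evidence that the trial's blinding has failed.

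**What to change.** Take the satisfaction questionnaire out of the week-8 face-to-face visit. Send it by the e-mail and online route already used for the PHQ-9 and RDQ, either after the week-8 HDRS, CGI and FAST ratings are locked in the e-CRF or together with the 12-week online follow-up. Keep it and its responses out of the assessor's view. Move the mark in Table 2 accordingly and add a sentence to the Procedure section.

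If the form has to stay at the visit, the least that protects the HDRS is to state that someone other than the assessor gives it out after the ratings are locked. No later HDRS is scheduled, so for the primary outcome the order alone would suffice if it is kept; the online route is safer because it does not depend on each site keeping to that order.

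The cost is one form moved to a system already in use. Response to this descriptive measure may be slightly lower, and with the 12-week option participants would answer longer after finishing the programme. No other outcome or analysis changes.
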